## 5. STUDY DESIGN

**Design:** 2 x 2 factorial design, multi-centric, open labelled, randomized controlled trial

**Total study duration:** 36 months

**Number of scheduled visits:** 5

- (i) **Screening visit (visit -2,  $\leq 16$  weeks GA):** Singleton pregnant women willing to participate in the study will be assessed for eligibility based on inclusion/exclusion criteria and eligible participants will be asked to sign an informed consent if willing to participate. Eligible women will undergo an oral glucose tolerance test (OGTT) to rule out impaired glucose intolerance or diabetes at screening and will also undergo dating ultrasound scan. Routine antenatal examination will be done. Barriers to life-style interventions-1 during pregnancy will be assessed using a questionnaire.
- (ii) **Run-in visit (visit -1,  $\leq 17$  weeks GA):** Baseline assessments of dairy product consumption will be done using standardized questionnaire. Additionally, objective measurements of baseline PA activity over 7 days will be assessed in all study participants (with the result blinded to participants) using a wearable accelerometer device (Garmin Vivofit 4 fitness band).
- (iii) **Randomization ( $\leq 18$  weeks GA):** Women will be randomized to either (i) diet (consumption of 200g of yoghurt per day), (ii) PA (a minimum of 40% increase above the recorded baseline PA) (iii) diet and PA or (iv) standard care. Active intervention will be from randomization to 32 weeks of GA.
- (iv) **Visit 1 (18-20 weeks GA):** maternal weight, blood pressure, routine antenatal examination and foetal morphology scan.
- (v) **Visit 2 (26-28 weeks GA):** maternal weight, blood pressure, routine antenatal examination and OGTT. Primary endpoint (diagnosis of GDM based on IADPSG criteria) will be assessed at this visit. Women with GDM will continue on allocated study intervention until end of study (week 32) in addition to the clinical management provided as per the local obstetric practice.
- (vi) **Visit 3 (32 weeks GA, End of Study visit):** maternal weight, blood pressure, routine antenatal examination, ultrasound foetal scan and fasting blood glucose and barriers to pregnancy intervention-2 assessment. (A repeat ultrasound scan at this stage is based on the evidence that growth restriction although starts in early pregnancy, is more marked between 22-34 weeks and also that foetal measurements do not have

Date and version No: 18th July 2019, Version 4.2

exact equivalents to new born measurements. Therefore, a last trimester scan is essential as it reflects foetal growth more precisely).

- (vii) **Delivery visit:** This is a post-trial surveillance visit primarily intended to assess the safety and efficacy of interventions on pregnancy and new-born outcomes.

Aside from the scheduled study visits, participants will be contacted on a weekly basis either over telephone or visited at home by research personnel. This will be made to ensure general well-being, compliance (wearing device, adhering to individually advised increment in step count, reminders of study visits, yoghurt consumption etc) and motivation.

### Interventions

**Dietary intervention** Each participant in the diet and diet+PA arm will be advised to consume yoghurt 200 g/day once daily prepared locally at the dietary department in CMC, Vellore and from a local production in The Gambia. The yoghurt consumption is independent of the timing of their regular meal time (can be consumed anytime). Record of daily yoghurt and background dairy consumption will be maintained by every participant. The yoghurt will be prepared on a common recipe with the same starter culture at both centres. The yoghurt will be dispensed daily/weekly as feasible by the study centre. Adherence to yoghurt consumption will be monitored on a weekly basis by home visiting field staff. Dietary counselling will be reinforced in all participants and the non-diet arm will not be advised to stop their regular dairy consumption, assuming that any effect on outcome is related to the trial yoghurt consumed.

**Physical activity intervention** Women randomized to the PA and diet+PA arm will be provided PA targets to be followed throughout pregnancy based on their baseline PA assessment which was obtained at run-in-phase. The recommendation will be set based on a minimum of a 40% increase of the baseline step count measured during run-in-phase (refer to section 8.1.2 for details). The daily PA activity will be monitored using an accelerometer device (Garmin Vivofit 4 fitness band) which will provide visual feed back to the participants in the active PA arms in order to motivate participants and help them achieve their daily target step count. All other (yoghurt and standard arm) will also be provided with fitness bands to objectively measure their routine PA behavior throughout the study. However, step counts will be blinded for these participants. Data from these devices will be periodically uploaded using vivohub 2 for compliance monitoring and downloaded to provide visual feedback and counselling to participants.

### Potential risks and benefits

#### Risks with study-related procedures

Risks with venepuncture may include bruising in the area of venipuncture, dizziness, nausea, vasovagal syncope. Consumption of oral glucose solution on an empty stomach may cause nausea, vomiting, headache. Ultrasound scans during pregnancy are not considered harmful. Utmost care would be taken to minimize such risks. A trained phlebotomist or research nurse will draw blood samples for the study. We will use clean, sterile phlebotomy equipment. Blood will be drawn using vacutainers with women sitting or lying down, whichever is comfortable. Local pressure will be applied for 20-30 seconds to avoid post-puncture bleeding.

Date and version No: 18th July 2019, Version 4.2

### Risks with interventions

There are no major serious adverse effects directly linked to the proposed interventions in the study. Both yoghurt and PA are generally considered safe during pregnancy. However, some potential adverse effects of the proposed interventions can be anticipated and are not necessarily caused by or related to the intervention. In the yoghurt consumption arm, anticipated risks may include nausea, vomiting and intolerance to yoghurt. In women undertaking physical activity, common adverse effects may include dizziness, headache, exertional dyspnoea, easy fatigability and muscle aches. The proposed PA in our study meet the safety guidelines for physical activity recommended by the ACOG (27). Safety will be ensured by excluding women who have absolute contraindications to aerobic physical activity during screening. Potential risks of PA may include persistent vaginal spotting/bleeding, calf pain/swelling (diagnosed to be related to thrombophlebitis or deep vein thrombosis), dyspnoea at rest, painful premature contractions, decreased foetal movements, preterm labour and preterm/premature rupture of membranes. A participant will be withdrawn from the study, in the event of persistent adverse events reported by the participant, and the PI feels that the event may be related to the intervention.

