## 7.6. Subsequent Visits

### 7.6.1. Visit 1 (week 18-20)

- I. **Weight:** Weight of the mother will be recorded as described in 7.5.1 (II)
- II. **Blood pressure:** Systolic and diastolic BP of the mother will be recorded as described in 7.5.1 (III)
- III. **Antenatal examination (fundal height):** Routine antenatal examination including fundal height will be recorded as described in 7.5.1 (IV)
- IV. **Safety assessments** to interventions (e.g. adverse events and/or SAE assessment).
- V. **Concomitant medication** assessment
- VI. **Compliance assessment:** to interventions (step count, yoghurt diary)
- VII. **Morphology scan:** The following variables would be measured and recorded:  
Gestational age, bi-parietal diameter, head circumference, femoral length, Abdominal circumference, estimated foetal weight, liquor amount, placenta: anterior/posterior and upper segment/lower segment, amniotic Fluid Volume Index, Uterine artery Doppler: Pulsatility Index, Systolic/diastolic ratio, gross anomalies in region of head and neck (transcerebellar plane, transventricular plane, biparietal plane, nose/lips), thorax (lungs, 4 chamber view, outflow tract, diaphragm), Spine, Abdomen (stomach bubble, kidneys, cord insertion, number of vessels in cord, genitalia, limbs). Participants with any foetal congenital anomaly, placental malformation or malposition or abnormal ultrasound features that can compromise pregnancy outcome according to the investigator will be withdrawn from the study at this stage.

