## 7.8. Discontinuation/Withdrawal

Discontinuation/withdrawal has to be distinguished from i) discontinuation from the study (interventions, follow-up visits, study-related procedures) and ii) discontinuation from interventions only and could occur under following circumstances

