### 7.8.1. Discontinuation/Withdrawal from the study

Discontinuation from the study occurs

- When a participant voluntarily withdraws consent to further participation at any time during the trial.

Date and version No: 18th July 2019, Version 4.2

- Significant protocol deviation such as Ineligibility (either arising during the study or retrospectively having been overlooked at screening)
- Loss to follow-up

Details of withdrawing/discontinuation from the study prior to completion of all scheduled visits should entered in the “study termination form”

Participants who are diagnosed to have GDM (by laboratory evidence within the protocol or outside diagnosis confirmed by an OGTT at study centre) should continue interventions till week 32 (end of study visit), unless there is a safety concern.

Temporary or permanent discontinuation of interventions (as detailed in sections 7.8.1 and 7.8.2) for safety reasons will not lead to withdrawal of the participant from the trial. Withdrawal of the participants will not be replaced by recruitment of new participants. The primary reason for withdrawal will be specified in the Case Report Form.

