##### **7.8.2.2. Permanent discontinuation/withdrawal from interventions**

Permanent discontinuation from intervention is any intervention discontinuation associated with the definitive decision from the Investigator not to re-expose the participant to the either yoghurt or PA or both at any time during the study. This may occur during situations of **unexpected SAE**, where, in the investigator's opinion, continuation with intervention would be detrimental to the participant's well-being

Examples of permanent discontinuation could be

- development of blood pressure 150/100 mmHg anytime during the trial
- Hospitalisation due to medical event (only if further continuation of interventions will affect maternal or new born health)
- Anaemia diagnosed based on haemoglobin <10g/dl
- Ultrasound evidence of major degree placenta previa

Participants will be followed-up according to the study procedures specified in this protocol up to the scheduled date of study completion. It is important to collect data on all participants, regardless of intervention, during the entire duration of the study as all data until the scheduled date of study completion will be used in statistical analyses.

In case the participant decides to withdraw participation or consent during the study, we will not work on participant's samples without permission, but any information already generated from the samples until the time of withdrawal will be used and samples already collected, for which they have given consent, will also be analysed and data used.

Date and version No: 18th July 2019, Version 4.2

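### Sections 5 and 7.6.1 withdraw randomised women from the study where sections 7.8.1 and 7.8.2.2 keep them in follow-up, so primary outcomes can go uncollected

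*Protocol*

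**What the plan says.** Section 7.8 separates two things: stopping the interventions only, and "discontinuation from the study (interventions, follow-up visits, study-related procedures"). The second therefore ends outcome visits as well.

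Three rules place randomised women in the second category:

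- **Adverse events (section 5, Risks with interventions).** "A participant will be withdrawn from the study, in the event of persistent adverse events reported by the participant". The rule applies where the PI suspects the intervention as a cause.
- **Scan findings (section 7.6.1, Visit 1, week 18-20).** The rule covers a foetal anomaly and a malformed or malpositioned placenta. It also says that women with "abnormal ultrasound features that can compromise pregnancy outcome according to the investigator will be withdrawn from the study at this stage".
- **Ineligibility (section 7.8.1).** The reasons for leaving the study include "Significant protocol deviation such as Ineligibility (either arising during the study or retrospectively having been overlooked at screening").

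Other text keeps comparable women in. Section 7.8.1 says that temporary or permanent discontinuation of interventions "for safety reasons will not lead to withdrawal of the participant from the trial". Section 7.8.2.2 lists "Ultrasound evidence of major degree placenta previa" among its examples of stopping the intervention permanently. It then requires follow-up to the scheduled end of study, and adds: "It is important to collect data on all participants, regardless of intervention, during the entire duration of the study". Section 10.1 names intention-to-treat as an analysis principle.

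**The concern.** A site that meets a persistent, possibly related adverse event, or a malpositioned placenta at Visit 1, has two instructions. One ends follow-up and the other requires it. The choice lies with an investigator who knows the allocation, because the trial is open-label (section 7.4).

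The primary outcome needs the OGTT at 26-28 weeks and the fasting glucose at 32 weeks. If the withdrawal instruction is followed, those samples may never be taken, and no later analysis plan can recover them. Withdrawn women are not replaced (section 7.8.1).

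The adverse-event rule depends on suspected relation to the intervention. It will therefore act mainly in the yoghurt, PA and yoghurt + PA arms, and the loss can differ between the arms being compared. The scan is done in every arm, so that route is not differential by construction, but it rests on unblinded judgement.

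**Working it through.** **1. The passages side by side**

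| Event after randomisation | Withdrawn from the study | Retained |
|---|---|---|
| Persistent AE, possibly related | Section 5 | Section 7.8.1, safety sentence |
| Placental malposition on scan | Section 7.6.1 | Section 7.8.2.2, major placenta previa |
| Ineligibility arising or found late | Section 7.8.1 | Section 7.8.2.2, data on all participants; section 10.1, intention-to-treat |

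The first two rows are direct contradictions. In the third, the safety sentence does not mention ineligibility. The conflict there is with the general data rule and the analysis principle.

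**2. When the outcome is lost**

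Visit 1 is at 18-20 weeks and the OGTT at 26-28 weeks, so a Visit 1 withdrawal carried out as written always loses the primary outcome. The other two routes lose all of it if they act before the OGTT, and the 32-week component if they act between the two tests. The termination assessments in section 7.6.3 are worded for voluntary withdrawal and include a fasting glucose but no OGTT.

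**3. Does the 15% allowance cover it?**

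Section 10.2 counts drop-outs as non-compliers at 25% GDM risk whose outcome is still observed. The planned cell risks are 25%, 16.75%, 16.75% and 11.2% (25% × 0.67² = 11.22%).

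- Margins before dilution: (25 + 16.75)/2 = 20.875% and (16.75 + 11.22)/2 = 13.99%.
- With 15% at 25%: 0.85 × 20.875 + 3.75 = 21.49% and 0.85 × 13.99 + 3.75 = 15.64%.
- Power with 928 per margin and two-sided alpha 0.025 is 84.3%. If each effect must also pass its own country-interaction test at 5%, it is about 0.843 × 0.95 = 80.0% (80.8% in 10,000 simulated trials). This reproduces the plan's 80% at 1,856.

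Missing outcomes come on top of that. At assumed losses of 5%, 10% and 15%, equal in all arms, the same simulation gives 78.7%, 76.7% and 73.5%.

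**4. Bias from the adverse-event route**

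The protocol gives neither a withdrawal rate nor the GDM risk of withdrawn women. Assume no true effect, a risk of 0.21 (section 10.2's 20.9%, rounded), and a fraction f removed from each of the three active arms, with GDM risk q among those removed. For either factor, both arms of the treated margin lose f. The comparator margin is standard care, which loses nothing, plus the other single-intervention arm, which loses f. Overall it loses f/2.

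- Treated margin: (0.21 − f·q)/(1 − f)
- Comparator margin: (0.21 − f·q/2)/(1 − f/2)

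| f | q | Treated | Comparator | RR |
|---|---|---|---|---|
| 5% | 0.30 | 0.195/0.95 = 0.2053 | 0.2025/0.975 = 0.2077 | 0.988 |
| 5% | 0.40 | 0.190/0.95 = 0.2000 | 0.2000/0.975 = 0.2051 | 0.975 |
| 10% | 0.30 | 0.180/0.90 = 0.2000 | 0.195/0.95 = 0.2053 | 0.974 |
| 10% | 0.40 | 0.170/0.90 = 0.1889 | 0.190/0.95 = 0.2000 | 0.944 |

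The sign depends on q. Taking q as far below 0.21 as 0.30 is above it (q = 0.12):

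- f = 5%: (0.204/0.95)/(0.207/0.975) = 1.011
- f = 10%: (0.198/0.90)/(0.204/0.95) = 1.025

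**The case against.** The case on the other side is that this is a wording conflict with limited consequences. Much of it stands.

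- **Intention-to-treat.** A reader might infer that it is broken or cannot be done. The protocol does not say so. Nothing removes withdrawn women from the analysis set, section 7.8.2.2 uses data already generated, and the handling of missing outcomes can be set in the SAP. What remains is that the outcome is not collected.
- **Size of bias.** A reader might compare a depleted treated margin with an intact comparator and get risk ratios of 0.98-0.95 at 5% removal and 0.95-0.90 at 10%. That ignores the factorial layout, in which half of each comparator margin also receives an intervention. Section 5 anticipates no major serious effects linked directly to the interventions, so removal rates of 5-10% have no support in the protocol. Neither does a 30-40% GDM risk among removed women.
- **Outcome-dependent removal.** Gestational hypertension is both an exclusion criterion and a surveillance outcome. A reader might infer that women are withdrawn because they develop it. Section 7.8.2.2 treats a blood pressure of 150/100 as an intervention-only stop, and section 7.8.1 keeps women with GDM on intervention to week 32. The protocol has therefore settled the primary outcome, and hypertension at that threshold.
- **Always missing, and only in active arms.** Neither holds in general. Adverse events or ineligibility may come after the OGTT. The adverse-event route falls mainly, not exclusively, on active arms.

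These points reduce the size of the problem. They do not reconcile sections 5 and 7.6.1 with sections 7.8.1 and 7.8.2.2.

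**Conclusion.** The concern holds as an internal contradiction with a consequence for the data. For adverse events and placental findings, the protocol both ends and continues follow-up. For ineligibility, it ends follow-up despite a rule to collect data on everyone. Followed as written, sections 5 and 7.6.1 and the ineligibility item can leave the primary outcome uncollected after randomisation, and the sample size makes no allowance for that.

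The contradiction rests on the text alone. Its numerical effect rests on assumptions. With no true effect, a 21% risk and equal removal from the three active arms, the spurious reduction is about 1-2.5% at 5% removed and 2.5-5.5% at 10%, if removed women have a 30-40% GDM risk. It becomes a spurious increase if their risk is below average. The power losses likewise depend on assumed loss rates, and on each effect being tested against its own interaction. If a significant interaction for either intervention blocks both effects, power starts at about 76-77% rather than 80.8%.

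**What to change.** Reconcile sections 5, 7.6.1, 7.8.1 and 7.8.2.2 under one rule. Adverse events, scan findings and ineligibility arising or found after randomisation may end the intervention, on clinical criteria that the investigators set, but they do not end outcome collection. A woman who has not withdrawn consent and whose pregnancy continues keeps the scheduled 26-28 week OGTT, the 32-week fasting glucose and the delivery data, and is analysed as randomised.

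In practice, section 5 and the last sentence of section 7.6.1 would refer to stopping the intervention rather than leaving the study, and the ineligibility item would move out of the list of reasons for leaving the study. The investigators should also state how the placental findings in 7.6.1 relate to the placenta previa example in 7.8.2.2.

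The cost is an amendment of a few sentences. The visits are already in the schedule (Appendix C), and 1,856 does not change. OGTTs missed before the amendment cannot be recovered.

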### 7.6.3. Visit 3 (Week 32) - END OF STUDY VISIT

- I. **Weight:** Weight of the mother will be recorded as described in 7.5.1 (II)
- II. **Blood pressure:** Systolic and diastolic BP of the mother will be recorded as described in 7.5.1 (III)
- III. **Antenatal examination (fundal height):** Routine antenatal examination including fundal height will be recorded as described in 7.5.1 (IV)
- IV. **Fasting plasma glucose**
- V. **Barriers** to pregnancy intervention-2 assessment
- VI. **Ultrasound scan:** The ultrasound scan would be done during visit 3 (week 32) in all participants which would include measurement of bi-parietal diameter (BPD), head circumference, femoral length, abdominal circumference, estimated foetal weight, liquor amount, placenta: anterior/posterior and upper segment/lower segment, amniotic Fluid Volume Index, Uterine artery Doppler: Pulsatility Index, Systolic/diastolic ratio.
- VII. **Safety assessments** to interventions (e.g. adverse events and/or SAE assessment) and review of concomitant medications.
- VIII. **Compliance assessment:** to interventions (step count, yoghurt diary) & close of interventions.

In the event the participant withdraws from the study at any time prior to week 32 visit, then the date of voluntary withdrawal will be marked as "END OF STUDY VISIT". The participant will undergo all assessments as listed in 7.6.3 except morphology scan.

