## 10.2. The Number of Participants

The sample size is 1856 high-risk women (928 to be recruited in The Gambia and India). The study was powered to have 80% to detect a 33% reduction in the incidence of GDM, for the main effects of diet and PA, with a family-wise significance level of 5% for a two-sided test (i.e. each effect was tested at a significance level of 2.5%). It was assumed that participants could be pooled across centres (no interaction between interventions and country at the 5% level). The sample size was inflated to allow for a 15% drop out rate in each of the four strata, with drop outs defined as non-compliant participants (i.e. no risk reduction in their incidence of GDM).

The effect sizes for the sample size calculation were:

Prevalence of GDM in high-risk pregnant women: The largest study of GDM women (The HAPO study, 25,505 pregnant women unselected for GDM risk at 15 centres in nine countries) reported a GDM prevalence rate, based on IADPSG criteria, of 17.8% among the general population. In our 'high-risk' population, we assume that the prevalence will be higher than in the HAPO study. Therefore, we have estimated the prevalence of 25% in our study.

Estimated risk reduction: A recent meta-analysis (Song et al. Obesity reviews 2016) has shown that either diet or PA results in 18% (95% CI 5-30%) risk reduction in GDM in general pregnant population and interventions as early as 15 weeks of gestational age was also associated with reduced GDM risk (Relative risk: 0.80, 95%CI 0.66-0.97). Putting all these together, we estimate the risk reduction would be higher (about 1/3, 33%) in this high-risk population. We modelled the GDM percentages in four equal-sized combinations of control (c) and treatment (t) arms as 25% (c-c), 16.75% (c-t and t-c) and 11.2 in t-t group. Therefore, in simple comparisons of one exposure, the percentages will be 20.9% vs 13.0%.

Absence of intervention\*country interaction: In order to pool the participants of both countries, we will be assuming that there are no differences between the participants of both countries. This initial test for a non-significant interaction term (at the 5% level) between each intervention and country was also taken into account in the sample size simulation.

The sample size calculation was performed by simulation (in R version 3.5.2) according to the following algorithm:

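### Section 5 withdraws women with persistent, possibly related adverse events from the study, while section 7.8 stops only their intervention and keeps them in follow-up

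*Protocol*

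**What the plan says.** Two parts of the current protocol (version 4.2) tell the site what to do with a woman who has lasting adverse effects.

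- **Section 5, Risks with interventions:** "A participant will be withdrawn from the study, in the event of persistent adverse events reported by the participant", on the condition that "the PI feels that the event may be related to the intervention".
- **Section 7.8:** distinguishes "discontinuation from the study (interventions, follow-up visits, study-related procedures" from stopping the intervention alone.
- **Section 7.8.1:** gives three grounds for leaving the study: withdrawn consent, significant protocol deviation such as ineligibility, and loss to follow-up. Adverse events are not among them. It adds that stopping an intervention, temporarily or permanently, "for safety reasons will not lead to withdrawal of the participant from the trial".
- **Section 7.8.2.2:** keeps women who stop permanently in follow-up to their scheduled completion, and gives the reason: "It is important to collect data on all participants, regardless of intervention, during the entire duration of the study".

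A related pair concerns scan findings. At the 18-20 week scan, section 7.6.1 says that women with "placental malformation or malposition or abnormal ultrasound features that can compromise pregnancy outcome according to the investigator will be withdrawn from the study". Section 7.8.2.2 lists major placenta previa as a reason to stop the intervention only.

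**The concern.** The same woman leaves the study under section 5 and stays in it under section 7.8. Section 5 cannot be read loosely as meaning withdrawal from the intervention, because section 7.8 exists to keep those two things apart.

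The primary outcome needs the OGTT at 26-28 weeks or the fasting glucose at 32 weeks. A woman withdrawn before visit 2 has neither, and section 7.8.1 says withdrawn women are not replaced. The trigger is a judgement, made without blinding, that the event may be due to an intervention. Standard care has no intervention to blame, so outcomes would go missing by arm, which is what intention-to-treat follow-up is meant to prevent.

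Safety information is at risk too. Section 5 names preterm labour and rupture of membranes as potential risks of physical activity, and preterm birth is recorded at delivery. Women withdrawn for such reasons are those whose delivery outcomes matter most.

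**Working it through.** **The text.** No stated figure is in dispute, so the first step is to follow one case: a woman in a physical activity arm with a persistent, possibly related adverse event at 22 weeks.

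| Step | Section 5 | Section 7.8 |
|---|---|---|
| Intervention | ends | interrupted or stopped |
| Visits 2 and 3 | end with study participation | continue |
| Primary outcome | missing | observed |

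**Does the early-exit visit repair this?** No. Section 7.6.3 says "The participant will undergo all assessments as listed in 7.6.3 except morphology scan", but that provision is written for voluntary withdrawal. Its list has a fasting glucose and no OGTT, and the sample would fall outside the two protocol time points.

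**Does the sample size allow for it?** No. Section 10.2 inflates for a "15% drop out rate in each of the four strata, with drop outs defined as non-compliant participants". The simulation keeps those women in the analysis at a 25% GDM risk, at the same rate in every stratum. That models non-compliance. It does not model missing outcomes concentrated in treated arms.

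**Illustrative size.** Inputs from section 10.2: 1,856 women, so 1,856/4 = 464 per arm and 928 on each side of a main-effect comparison; arm risks 25% (neither), 16.75% (either one) and 11.2% (both). Assumed: a share *w* of each of the three intervention arms is withdrawn before visit 2 and none in standard care, with *w* from 1% to 5%; withdrawn women have a 25% risk, the value the protocol gives its own drop-outs.

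*Women lost.* The treated side loses 928*w*. The other side loses 464*w*, because one of its two arms receives the other intervention.
- *w* = 1%: 9.3 v 4.6, a gap of 0.5 percentage points of 928.
- *w* = 5%: 46.4 v 23.2, a gap of 2.5 points.
- If only the two physical activity arms are affected, that comparison loses 9.3 to 46.4 v 0 (1 to 5 points), and the yoghurt comparison is balanced (4.6 v 4.6 to 23.2 v 23.2).

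*Risk ratio with everyone followed.* Each intervention arm has risk (1 − *w*) × arm risk + *w* × 25%.
- *w* = 1%: treated (16.8325 + 11.338)/2 = 14.09%; other side (25 + 16.8325)/2 = 20.92%; ratio 0.673.
- *w* = 5%: treated (17.1625 + 11.89)/2 = 14.53%; other side (25 + 17.1625)/2 = 21.08%; ratio 0.689.

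*Risk ratio with withdrawn women missing.* The treated side is (16.75 + 11.2)/2 = 13.975%. The other side is [25 + (1 − *w*) × 16.75]/(2 − *w*).
- *w* = 1%: 41.5825/1.99 = 20.90%; ratio 0.669.
- *w* = 5%: 40.9125/1.95 = 20.98%; ratio 0.666.

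The benefit is overstated by 0.005 (1%) to 0.023 (5%). If withdrawn women instead kept their own arm's risk, full follow-up would give 13.975/20.875 = 0.669 and the overstatement would shrink to between 0.001 and 0.003.

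**The case against.** The best defence is that section 7.8 is the operative procedure and already has the right rule, while the section 5 sentence closes a descriptive paragraph on risks. Staff handling a real withdrawal would probably turn to 7.8. The section 5 trigger is also narrow, since the event must be both persistent and possibly related, and the protocol regards both interventions as generally safe in pregnancy. A woman withdrawn after visit 2 already has her OGTT and loses at most the 32-week glucose.

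The size is also small. On the log scale the shift is ln(0.673/0.669), about 0.007 from unrounded ratios, to ln(0.689/0.666) = 0.034. The standard error of the log risk ratio is √[(1 − 0.13975)/(928 × 0.13975) + (1 − 0.209)/(928 × 0.209)], about 0.10, so the bias is roughly 0.07 to 0.33 standard errors. Power hardly moves: an approximation that applies 15% non-compliance and one 5% country-interaction test per effect gives 80.0% with no one lost, 79.7% with 2% of the treated side lost and 79.0% with 5%.

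All of this limits the weight of the point. It does not remove the conflict: section 5 is a firm instruction in current text, and nothing says which section prevails. Nor could a statistical analysis plan recover an OGTT that was never done.

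The placental conflict is weaker. The two sections can be read as covering different stages of pregnancy, although major previa seen at 18-20 weeks falls under both. It applies to all four arms, so it loses outcomes without doing so unevenly.

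**Conclusion.** The contradiction is real and should be corrected. Section 7.8 states the right rule, and section 5 as written would remove women from outcome follow-up for reasons tied to treatment. The size cannot be known from the protocol. Under the assumed 1% to 5% loss before visit 2, confined to the intervention arms and with a 25% risk in those lost, the main-effect risk ratio is overstated in favour of the intervention by 0.005 to 0.023. The problem is avoidable bias; lost power is minor. The section 7.6.1 overlap on placental findings is secondary.

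**What to change.** Reword the section 5 sentence along these lines: *If adverse events persist and the PI considers them possibly related to an intervention, that intervention is stopped and the woman stays in follow-up as set out in 7.8.2.2, unless she withdraws consent.*

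Align section 7.6.1 in the same way, so that placental malposition found after randomisation stops the intervention but not outcome follow-up, unless consent is withdrawn.

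The cost is one sentence in each section and a memo to both sites. No assessment is added, and stopping an intervention for safety is unaffected. The small downside is that women who would have left must still be asked to attend visits 2 and 3, and some may decline.
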